# events a1i a0i Mi

Person-years N1i N0i Ti

______________________________________________________________________________

The Mantel-Haenszel rate ratio19 is given by

RR=[a1iN0i/Ti] / [a0iN1i/Ti].

The variance of the ln(RR) is given by20

Var[ln(RR)] = [MiN1iN0i/Ti2] / [(a1iN0i/Ti)(a0iN1i/Ti)].

The 95% CI for RR is as follows:

lower = exp[ln(RR) – zval * Var(ln(RR))1/2

upper = exp[ln(RR) + zval * Var(ln(RR))1/2,

where zval is the value from the standard normal distribution whose value will depend on the time of the analysis (see subsection on Interim Analyses).

If the 95% CI for RR does not include the value one, then we will reject the null hypothesis.

The analyses described above for the cumulative incidence of symptomatic advanced disease will also be performed for disease-specific mortality and all-cause mortality.

A Cox proportional hazards model will be fit to compare the two study arms on the time from randomization until symptomatic disease. Covariates will be included in the model, such as age, gender, race, smoking history, symptoms at presentation, as well as site of enrollment. A significance level of 0.05 will be applied.

13.3 **OTHER ANALYSES:**

In the intervention arm, for each screening, we will report the number of subjects with actionable findings and the type of findings. We will report the follow-up results of these findings. This will provide data on the false positive rate and the size and stage of detected cancerous nodules.

We will test the effect of CAD on radiologist performance. This will include the effect of CAD on the radiologists’ sensitivity, as well as the effect on the false positive rate. First, we will separate the screened cases into one of three groups based on follow-up results, as available: cancerous nodule(s) present, benign nodule(s) present and no cancerous nodules present, no nodules present. For each group we will compare the frequency with which radiologists reported an actionable nodule without CAD versus with CAD. For each group the frequencies will be compared using a McNemar’s test, modified for clustered data.21  The modification is necessary because two radiologists will be interpreting each case. A significance level of 0.05 will be applied.

14.0 **SAMPLE SIZE CONSIDERATIONS**

The following assumptions were made for determining the required sample size for the primary study aim: prevalence of cancer at baseline screen=1%; annual incidence of cancer=0.5%; annual lost to follow-up=10%; 90% of people randomized to screening are compliant at each screening; 12-month recruitment period; 1 incident screen planned for 12 months after the initial prevalence screen; and 85% sensitivity of chest x-ray with CAD. For development of symptoms following the development of preclinical disease, we assume a uniform distribution over 30 months so that the average time is 16 months from development of detectable preclinical disease until development of symptoms. We assume a 70% reduction in the development of advanced-stage cancers if preclinical disease is detected at screening.

*Placebo Arm:*

Based on these assumptions, if N patients are randomized to the placebo arm, then after one year the number of symptomatic, advanced-stage cancers will be:

(1-lost-to-follow-up rate)(prevalence) (rate of development of symptoms over 12 months)(N).

Similarly, at year two the number of symptomatic, advanced-stage cancers will be approximately:

(1-lost-to-follow-up rate)2 (prevalence) (rate of development of symptoms over 24 months)(N)

for those with preclinical disease at the time of enrollment.

In addition, there are

(1-lost-to-follow-up rate)(incidence)(rate of development of symptoms over 12 months)(N’)

symptomatic, advanced-stage cancers from those who develop lung cancer within the first year, where N’=N-(N)(prevalence).

*Screened Arm:*

If N patients are randomized to the screening arm, and if we assume that at the time of baseline screening, 30% of detected preclinical disease is advanced-stage cancer, then the number of detected advanced-stage cancers detected at baseline is M, where

M = (prevalence)(sensitivity) (0.30)(N).

After one year the number of advanced-stage cancers will be approximately:

(1-lost-to-follow-up rate) (prevalence)(sensitivity)(rate of development of symptoms over 12 months) (N-M)(1-risk reduction due to early treatment) for those cancers detected at baseline but still progressed to symptomatic, advanced-stage cancers in one year.

In addition, there are those cancers undetected at baseline that progress to symptomatic, advanced-stage cancers in the first year:

(1-lost-to-follow-up rate)(prevalence)(1-sensitivity) (rate of development of symptoms over 12 months)(N-M).

At the one-year incident screen we assume that 15% of detected preclinical disease is advanced-stage cancers. Thus, at the incident screen, M’ advanced-stage cancers will be detected:

M’= (1-lost-to-follow-up rate)(compliance rate with screening)(incidence rate)(sensitivity) (0.15)(N’).

At year two, the number of symptomatic, advanced-stage cancers will be approximately:

(1-lost-to-follow-up rate)2 (prevalence)(sensitivity) (rate of development of symptoms over 24 months)(N-M)(1-risk reduction due to early treatment) for those with preclinical disease detected at the time of enrollment but still progressed to advanced-stage cancers by two years.

In addition, there are those cancers undetected at baseline that progress to symptomatic, advanced-stage cancers over 24 months: (1-lost-to-follow-up rate)2 (prevalence)(1-sensitivity) (rate of development of symptoms over 24 months)(N-M).

There are also cancers that developed over the first year, were detected at the incident screen, and became symptomatic, advanced-stage cancers during the second year:

(1-lost-to-follow-up rate)2 (compliance rate with screening)(incidence)(sensitivity)(rate of development of symptoms over 12 months)(N’-M’)(1-risk reduction due to early treatment).

Finally, there are cancers that developed over the first year, were undetected at the incident screen, and became symptomatic, advanced-stage cancers during the second year:

(1-lost-to-follow-up rate)2 (incidence)(1-sensitivity)(rate of development of symptoms over 12 months)(N’-M’).

Table 2 summarizes the number of advanced-stage lung cancers expected in the two study arms as a function of N.

| N, # subjects per study arm | # advanced-stage cancers in placebo arm | # advanced-stage cancers in screening arm | Total Number of advanced-stage cancers |
| --- | --- | --- | --- |
| 3000 | 35.6 | 23.2 | 58.8 |
| 3500 | 41.6 | 27.1 | 68.7 |
| 4000 | 47.5 | 30.9 | 78.4 |
| 4500 | 53.4 | 34.7 | 88.1 |
| 5000 | 59.3 | 38.7 | 98.0 |

We plan to fit a logistic regression model to describe the probability of advanced-stage lung cancer as a function of 1) patient age, 2) gender, 3) symptoms status at time of enrollment, and 4) study arm randomized to. We will also consider in the model all two-way interactions with study arm. The rule of thumb to avoid model overfitting is at least 10 events per independent variable in the model, thus we need at least 70 advanced-stage cancers (total) for the model building.

We estimate that if the frequency of advanced-stage cancers at two years is 1.19% for controls and 0.77% for the screened arm (difference of 0.42%), then we can detect this difference with 4000 subjects per study arm with 77% power (5% type I error rate, two-tailed test).

15.0 **COST-EFFECTIVENESS ANALYSIS**

The cost effectiveness analysis will be performed only on subjects who declare themselves as Cleveland Clinic patients at entry into the study. The rationale is based on experiences from other studies where it was found to be impossible to collect valid medical visit and hospital stay data from other medical institutions even when the study subject had signed a medical release form. Thus, it was decided that the cost-effectiveness assessment in this study would be limited to Cleveland Clinic patients for whom medical records could more easily and reliably be obtained. We recognize that this decision limits the generalize ability of our cost effectiveness analysis results.

This analysis will be conducted from the US societal perspective as recommended by the U.S. panel for cost effectiveness in health and medicine.24 The initial time horizon will be the three-year study period, but will also be extended to 10 and 20 years using Markov modeling approach to measure the long-term cost-effectiveness difference between lung cancer screening and placebo screening. When data are collected after each visit, the intermediate analysis will be conducted to analyze the short-term cost-effectiveness outcomes if necessary. The results from the intermediate study could be used to guide the concurrent treatment in clinical settings.

Two categories of data are collected for the cost-effectiveness analysis: cost data and effectiveness data. The cost data will include both direct cost and indirect cost for patients with screening or placebo screening. The direct cost will include costs of inpatient care, emergency-room visits, outpatient care, physician visits, and laboratory tests. The data will be collected by medical utilizations based on case report from (CRF). The cost of lung cancer screening by CAD chest x-rays will be included for patients in the screening group too. Current procedural terminology (CPT) and diagnosis related group (DRG) codes will be collected from the billing system for Cleveland Clinic internal visits. Codes for external visits will be assigned by healthcare institutions that treat our patients and can provide these codes to us. Otherwise, CPT and DRG codes will be determined by the project team based on the data collected on the medical utilization forms provided by the patient or their healthcare institutions. If a patient is hospitalized after randomization, the primary reason and length of stay will be collected too. This will be converted to a DRG code, which will be used to derive costs based on Medicare reimbursement amount. In addition, use of oxygen and the amount of oxygen use will be collected as prescription information, and the cost of oxygen will be calculated based on the standardized average wholesale price (AWP) reported in the Drug Topics® Red Book25. There is no reason to believe that the use of other prescription medications will differ significantly between the screening and placebo screening group. Thus the incremental cost is assumed zero and no additional prescription information will be collected.

The indirect cost comes from the loss of work or loss of productivity due to the screening and the diseases. From the society perspective, such costs associated with both patients and their family members or caregivers who take care of the patients will be collected. During each six-month visit, loss of work-days (hours) from the last visit to this visit will be collected including the time of hospitalizations, clinical visits, traveling to/from the clinic. The loss of productivity and time-related costs will be calculated as a product of days (hours) lost by their salary range determined at baseline. The indirect cost of caregivers will be collected in the same manner by multiplying the average salary and time spent from the caregivers. All cost data will be inflated to a common year using the medical care inflation indices from the Bureau of Labor Statistics (http//www.bls.gov).

A cost-effectiveness model developed in Treeage Data®26 pro suite will be utilized to investigate the cost effectiveness of lung cancer screening with chest x-rays and CAD in asymptomatic patients compared to the similarly profiled cohort of patients who receive placebo screening. The cost of all healthcare utilizations as calculated above will be included in the model. The health related quality of life (utility) results of the EQ-5D and paper standard gamble will be used as the effectiveness data so that results may be expressed as cost per quality adjusted life years (QALYs).27 Discount rates of 3% will be used for both costs and outcomes in this cost-effectiveness model, as recommended by the U.S. panel for cost effectiveness in health and medicine.24

The incremental cost effectiveness ratio (ICERs) will be calculated for the base analysis. Bootstrap simulation with replacement will be utilized to derive mean costs and utilities and associated ICERs with 95% confidence intervals.28 Acceptability Curves will be constructed to determine the probability of lung cancer screening being cost effective under certain cost-effectiveness thresholds.29 Conventionally, ICERs of less than $50,000 per QALY are considered very cost effective whilst those with an ICER of between $50,000 and $100,000 per QALY are considered moderately cost effective.30

The Markov decision tree model will be used to derive the long-term cost-effectiveness differences between lung cancer screening and placebo screening for 10 and 20 years. The transition cycle of the Markov model will be one year. The transitional probabilities between different disease states will be calculated from the collected incidence of the study. The cost and utility data of the Markov model will apply the data from the five-year study period by discounting of 3% as a base-case. Similarly, ICERs will be calculated and bootstrap simulation will be used to derive the 95% confidence intervals of the ICER.

Sensitivity analysis will be performed by varying costs and utilities by their 95% confidence intervals established in our study. The impact of varying the probabilities of the detection of pre-clinical disease and incidental findings will also be investigated in sensitivity analysis. Sub-group analysis will also be used to investigate the patient characteristics that could contribute to the most cost-effective use of screening, including age, gender, and smoking history.

16.0 **ADVERSE EVENTS**

The principal investigator/s will review all adverse events and unanticipated problems as related to the imaging research. Adverse events and unanticipated problems will be reported promptly per all institutional, FDA, state and Federal regulations. In addition, if the investigator and co-investigators as a group have any concerns, they will escalate those concerns to the outside advisory board for review and guidance.

Adverse event reporting is to be distinguished from the collection of data for purposes of analyzing trial endpoints, which is achieved through the recording of specific data elements on case report forms and statistical analysis.

Complications associated with primary interventions are termed direct AE's. Screening tests promote downstream diagnostic interventions: complications associated with these diagnostic interventions are termed indirect AE's. Primary interventions in this protocol are the screening chest x-ray or placebo. In this protocol only direct adverse events associated with the primary trial intervention (chest x-ray or placebo) will be reported as adverse events. Indirect adverse events (complications associated with these diagnostic interventions) will be documented as part of the endpoints on case report forms.

Potential expected and unexpected adverse events may include but are not limited to any injury or incident occurring to the patient while receiving the primary trial intervention or possibly accidental radiation exposure when a placebo was originally intended

For this protocol, the following AE's are specifically excluded from AE reporting unless they are related to the primary trial intervention (chest x-ray or placebo): Complications of the following conditions: hospitalizations, prolonged hospitalization, or surgeries should NOT be reported as an AE in this trial.

Complications from diagnostic procedures performed because of screening intervention: such as elective surgery or minimally invasive procedures for a pre-existing condition, therapy for lung cancer, death from lung cancer, death from other cancer or pre-existing condition. These conditions will be recorded on study report forms for the purpose of endpoint analysis.

17.0 **DATA SAFETY AND MONITORING COMMITTEE**

These members will meet at least once per study year by conference call and/or in person to review adverse events and interim analyses, and advise the research team.

18.0 **PATIENT CONSENT AND PEER JUDGEMENT**

All institutional, NCI, FDA, state and Federal regulations concerning informed consent and peer judgment will be fulfilled.

19.0 **REFERENCES**

2. Community Health Assessment and Center for Public Health Data and Statistics. 2002, Ohio Department of Health Columbus OH.
3. Annual Smoking Attributable Mortality; Years of Potential Life Lost and Economic Cost – United State – 1995/199, Morbidity and Mortality weekly report, MMWR, 2002. 51; pp.300-303.

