Chest x-rays will be interpreted by chest-radiologists. The radiologist will first read the case without CAD, and then with CAD. The findings will be reported by the radiologist on the Radiology Reading Form (case report form), which includes reader findings and recommendations for follow-up. If the radiologist does not find an actionable nodule and does not recommend follow-up for the subject, then the images will be read by a second chest radiologist. This second reading will be blinded to the first interpretation. The findings will be reported by the second radiologist on Radiology Reader Form (case report form). Subjects who underwent a chest x-ray and were found to have an actionable finding on the chest x-ray by one of the radiologists will be mailed a Findings Report form, along with the dictated medical record reports, via certified mail. The Findings Report form will include all actionable findings found by the radiologist. Chest x-rays will be interpreted and reported within approximately four to six weeks of the chest x-ray, and subjects with actionable findings will be notified shortly thereafter.

Subjects with actionable findings will be phoned after written notification to answer any questions the subject has, and to encourage a follow-up visit with a primary care physician or pulmonologist. The recommendations of the radiologist will not be mandated to the subject’s physician; rather, subjects and their physicians together will determine the plan for follow-up testing and treatment, as appropriate.

Subjects with no primary care physician will be offered a list of physicians who could receive the results of their positive screening and oversee the management of follow-up recommended as a result of screening. Under-insured participants will be offered information about local sources of financial assistance and health care services. We will limit the number of subjects that are uninsured at baseline to 10% to ensure that the study objectives are not compromised by an inadequate number of subjects who pursue recommended follow-up.

9.0 **ANNUAL SCREENINGS**

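### Section 13.3 sorts non-cancer cases into benign-nodule and no-nodule groups by work-up results that depend on the reading under test, so the within-group CAD reporting rates cannot be interpreted

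*Protocol*

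**What the plan says.** Section 13.3 (Other Analyses) sets out to test the effect of CAD on readers' "sensitivity, as well as the effect on the false positive rate". It fixes three steps.

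- Grouping: "we will separate the screened cases into one of three groups based on follow-up results, as available". The groups are cancerous nodule, benign nodule without cancer, and no nodule.
- Comparison: "For each group we will compare the frequency with which radiologists reported an actionable nodule without CAD versus with CAD".
- Test: "For each group the frequencies will be compared using a McNemar" test modified for clustering, and "A significance level of 0.05 will be applied".

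Section 8.0 determines who gets follow-up results. Subjects "found to have an actionable finding on the chest x-ray by one of the radiologists will be mailed a Findings Report form" and are phoned to encourage a visit to a physician. The work-up is optional: "The recommendations of the radiologist will not be mandated to the subject’s physician". A negative first reading leads to a second blinded reading of the same image, not to a diagnostic test. Section 9.0 repeats this for the incident screen.

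Some follow-up reaches everyone. Under Section 11.1 every participant completes six-monthly forms, and any reported lung cancer leads to a request for records, whatever the reading was. Section 9.0 plans one incident screen; under Section 4.0, those enrolled after December 31, 2009 have the baseline screen only. Table 1 also schedules a Nodule Form, whose content is not shown.

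**The concern.** Telling a benign nodule from no nodule requires a work-up. The protocol directs a subject to one only when a reader has called something actionable, so the reading helps to decide the group in which that same reading is then scored. This is partial verification. Almost every case confirmed as benign is one that a reader flagged. Benign nodules that both readers missed have no route into the benign group unless other care happens to reveal them; they are counted as no nodule or left out.

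The randomised comparison is chest x-ray with CAD against placebo, so it cannot isolate CAD. The Section 13.3 comparison is the planned analysis of what CAD itself adds. A published benign-group rate near 100% with CAD, and the with/without difference beside it, would misstate the cost of CAD in false positives.

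**Working it through.** The protocol gives no rate, power or sample size for the CAD analysis, so there is no figure to reproduce. What follows shows the mechanism and its possible size.

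**Inputs from the protocol.** 4,000 screened subjects, 1% prevalence and 85% sensitivity with CAD (Section 14.0). Benign nodules in 5% to 50% of participants (the only figure available, from the CT cohorts described in Section 2.0).

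**Assumptions not in the protocol.** Benign nodules are flagged at f0 = 0.30 without and f1 = 0.40 with CAD, or at 0.60 and 0.70. Subjects with no nodule are flagged at 0.03 and 0.04. Everything flagged without CAD is also flagged with CAD. Work-up reaches 100% or 70% of flagged subjects.

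**Benign group.** If only flagged cases are verified, the observed rate is f0/f1 without CAD and 1 with CAD. The observed gap is (f1 − f0)/f1, which is the true gap divided by f1.

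- 0.30/0.40 = 0.75, so 0.75 to 1.00 is observed: 25 points against a true 10.
- 0.60/0.70 = 0.86, so 0.86 to 1.00 is observed: 14 points against a true 10.

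Neither result depends on the share with benign nodules, or on the work-up share if that share is equal for all flagged cases.

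**No-nodule group** (true 0.030 to 0.040; benign flag rates 0.30 and 0.40). Cancer-free subjects number 4,000 × 0.99 = 3,960.

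- Read-negatives placed here, all flagged subjects worked up, 5% benign (198 with, 3,762 without): the group is 3,762 + 198 × 0.60 = 3,880.8. Rates are 112.86/3,880.8 = 0.029 and 150.48/3,880.8 = 0.039.
- Same handling, 50% benign (1,980 each): the group is 1,980 + 1,188 = 3,168. Rates are 59.4/3,168 = 0.019 and 79.2/3,168 = 0.025.
- 50% benign, 70% work-up, flagged subjects without work-up left out: the group is 1,900.8 + 55.44 + 1,188 = 3,144.24. Rates are 41.58/3,144.24 = 0.013 and 55.44/3,144.24 = 0.018.
- As the last case, but flagged subjects without work-up placed in this group: 1,980 × 0.40 × 0.30 = 237.6 benign cases join it, 178.2 of them flagged without CAD. Rates are (59.4 + 178.2)/3,405.6 = 0.070 and (79.2 + 237.6)/3,405.6 = 0.093.
- All unverified cases left out: 0.03/0.04 = 0.75 to 1.00, a 25-point gap against a true 1 point.

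The direction of the error therefore turns on a handling rule that Section 13.3 does not state.

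**What is not disturbed.** McNemar's test works from discordant readings. A case negative both ways is concordant, so losing it changes the denominator of the rates but not the discordant count. With full work-up the benign-group discordant count is 20 of 20 (5% benign) or 198 of 198 (50% benign). With 70% work-up it is 14 of 20 or 139 of 198.

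**Pooled over all cancer-free subjects.** At 5% benign the with-CAD rate is (79.2 + 150.48)/3,960 = 0.0580. Counting all missed cancers (40 × 0.15 = 6) as cancer-free gives 229.68/3,966 = 0.0579. At 50% benign the figures are 871.2/3,960 = 0.220 and 871.2/3,966 = 0.2197.

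**Sensitivity.** Of 40 baseline cancers, 34 are detected. If a share c of the 6 missed later surfaces, observed sensitivity is 34/(34 + 6c): 100% at c = 0, 92% at c = 0.5 and 85% at c = 1.

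**The case against.** The strongest defence has four parts.

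- **Follow-up exists for everyone.** A reader might infer that subjects read as negative never receive a follow-up result. The protocol does not support that: the six-monthly forms, the records requests and, for most, an incident screen apply whatever the reading. This stands for cancer status. It does not settle benign versus no nodule, because no diagnostic imaging is scheduled for read-negatives between screens.
- **An overall rate is within reach.** The opening of Section 13.3 reports, for each screening, how many subjects had actionable findings and what follow-up showed. With the number screened, a pooled rate follows and is nearly unbiased. So a reader who concludes that the trial's false-positive rates are wrong in general goes too far. But the formal CAD comparison is specified group by group, and no pooled with/without-CAD comparison is stated.
- **The test survives.** This stands if every positive is worked up. The protocol does not secure that: work-up is optional, and it is not said whether a finding called without CAD and withdrawn with CAD leads to notification.
- **Detail may sit in the statistical analysis plan.** Handling of unverified cases may well be there. The grouping rule itself, however, is written into the protocol, and the dependence on the reading follows from that rule.

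The analysis is also outside the objectives in Sections 3.1 and 3.2, which limits its weight.

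**Conclusion.** The point holds for the split between benign nodule and no nodule. Membership of those two groups depends on the reading under evaluation, so their reporting rates and with/without-CAD differences cannot be interpreted. In the benign group the difference is inflated by a factor of 1/f1: 2.5-fold (25 against 10 points) or 1.4-fold (14 against 10) on the assumed flag rates. In the no-nodule group the error may go either way.

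A reader might infer a general tenfold inflation by setting rates among flagged subjects against rates over all screened subjects. The protocol does not support that. It compares a conditional with a marginal rate and needs every unverified case to be dropped, which Section 13.3 does not say. Only under that handling does the no-nodule gap grow so far.

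Sensitivity is overstated only as far as missed cancers fail to surface in follow-up. The McNemar comparison is largely intact if positives are worked up. No primary or secondary endpoint is affected. The flag rates and work-up shares are assumptions; the selection mechanism is not.

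**What to change.** In Section 13.3:

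- Define each screened case as cancer or cancer-free from the follow-up planned for every subject: six-monthly forms, records requests and the outcome review of Section 12.2.
- State one window that the calendar allows, for example up to the next screen or the end of follow-up. A fixed 12 months would not fit: incident screens after March 2010 have less than that before March 31, 2011, and someone enrolled in December 2009 and rescreened about December 2010 would have roughly three months.
- Flag late incident screens and losses to follow-up (Section 14.0 assumes 10% a year), or handle them in a sensitivity analysis.
- Report and compare the false-positive rate with and without CAD over all cancer-free screened subjects, and sensitivity over all subjects with cancer.
- Keep benign versus no nodule as a description of worked-up subjects only.

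The cost is wording, with no added tests for participants. The formal comparison no longer separates benign nodules from no nodules. Cancers not diagnosed within the window count as cancer-free, and more of these will follow late incident screens.

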Subjects without a diagnosis of lung cancer and who are deemed to be able to undergo treatment for lung cancer if detected (i.e. no medical condition that would prevent the subject from undergoing treatment for lung cancer) will be scheduled for an annual screening (or placebo screening). A study trained research personnel will phone the study subject and set up an appointment. One incident screens/placebo screen per subject is planned.

At this annual visit, the study trained research personnel will administer the annual study forms (see table 1) to the subject and record the data online. The study trained research personnel will then give the radiologist technician the subject’s randomization number. The trained radiology personnel will locate the randomization number on the paper list in the chest x-ray rooms and determine whether the subject is to receive a chest x-ray or placebo.

The chest x-rays from the annual incident screen will be interpreted by chest radiologists. A radiologist will first read the case without CAD, and then with CAD. Subjects who underwent a chest x-ray and were found to have an actionable finding on the chest x-ray will be mailed a Findings Report form, along with the dictated medical record reports, via certified mail. The Findings Report form will include all actionable findings found by the radiologist. If the radiologists does not recommend follow-up for the subject; then the images will be read by a second chest radiologist. This second reading will be blinded to the first interpretation. The findings will be reported by the second radiologist on a Radiology Case Report Form. Chest x-rays will be interpreted and reported within approximately four to six weeks of the chest x-ray, and subjects with actionable findings will be notified shortly thereafter. Subjects and their physicians together will determine the plan for follow-up testing and treatment, as appropriate.

10.0 **SUBJECT FOLLOW-UP**

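### Section 13.3 builds the CAD test on two radiologists per case, but a second radiologist reads only after a negative first reading, so pooling all readings would generally bias sensitivity and false-positive rates downward

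*Protocol*

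**What the plan says.** Section 13.3 (Other Analyses) sorts screened cases by follow-up into three truth groups: cancer, benign nodules only, and no nodules. Within each group, "we will compare the frequency with which radiologists reported an actionable nodule without CAD versus with CAD". The test is McNemar's, modified for clustered data, at the 0.05 level, and the stated reason for the modification is "The modification is necessary because two radiologists will be interpreting each case".

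The reading procedure is set elsewhere:

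- **Section 8.0 (baseline), order of reading:** "The radiologist will first read the case without CAD, and then with CAD".
- **Section 8.0, trigger for a second reading:** "If the radiologist does not find an actionable nodule and does not recommend follow-up for the subject". Only in that event does another radiologist see the film.
- **Section 9.0 (annual screen), trigger:** "If the radiologists does not recommend follow-up for the subject; then the images will be read by a second chest radiologist".
- **Both sections, blinding:** "This second reading will be blinded to the first interpretation".

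Neither section provides a second reading of an image that the first radiologist called positive. Section 13.3 does not say how images read once and images read twice are to be combined.

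**The concern.** The reason given for the test is untrue under the protocol's own reading rule. This is more than a wording slip, because the number of readings an image receives depends on nearly the same call that the test analyses. A first-reader positive contributes one without/with pair; a first-reader negative contributes two.

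The clustering adjustment allows for correlation between readings of the same image when the variance is computed. It does not undo the fact that second readings come only from images already called negative. Blinding the second radiologist does not undo it either, since the images themselves are selected.

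Section 13.3 aims to report the effect of CAD on sensitivity and on the false-positive rate. Rates computed from such a mixture do not describe a radiologist reading an unselected screening film. They would look too low on sensitivity and too favourable on false positives.

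**Working it through.** The protocol gives no power or expected rate for the CAD comparison, so there is no figure to reproduce.

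**Inputs from Section 14.0:** 4,000 subjects per arm, 1% baseline prevalence, 85% sensitivity of chest x-ray with CAD. **Assumptions:** the 85% is a single radiologist's sensitivity; the with-CAD call decides whether a second reading follows; all readings are pooled.

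**Formula.** Let p1 be the first reader's positive rate with CAD in a truth group, and p2 the second reader's positive rate among the first reader's negatives. Then

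pooled rate = [p1 + (1 − p1) × p2] / [1 + (1 − p1)].

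This equals p1 only if p2 = p1, that is, if readers are independent given truth group. If the same images are hard for both readers, p2 < p1 and the pooled rate is too low.

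**Sensitivity.** 4,000 × 0.01 = 40 cancers. The first reader calls 40 × 0.85 = 34 (one reading each) and misses 6 (two readings each). That makes 34 + 12 = 46 readings, with 6/40 = 15% of cancers read twice. With 90% compliance the counts fall to 36, 30.6 and 5.4, and the share stays 15%.

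| Second reader finds, of the misses | Pooled with-CAD sensitivity |
|---|---|
| 0% | 0.85/1.15 = 73.9% |
| 20% | (0.85 + 0.15 × 0.20)/1.15 = 76.5% |
| 40% | (0.85 + 0.15 × 0.40)/1.15 = 79.1% |
| 60% | (0.85 + 0.15 × 0.60)/1.15 = 81.7% |
| 85% (independence) | (0.85 + 0.15 × 0.85)/1.15 = 85.0% |

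**False positives.** For an assumed first-reader rate of 10%, 90% of cancer-free images are read twice. The pooled rate is 0.10/1.90 = 5.3% if the second reader adds none, (0.10 + 0.90 × 0.05)/1.90 = 7.6% at 5%, and 10% under independence.

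**The difference between CAD and no CAD.** This was simulated with a probit model and 4 million cases. Here rho is the strength of a case effect shared by both readers, tau that of a case effect specific to CAD reading, and the within-reader residual correlation is 0.7. A second reading was kept only if the first with-CAD call was negative. All rates are assumed; differences were taken before rounding.

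| True rate without/with CAD | rho | tau | Pooled without/with | True difference | Pooled difference |
|---|---|---|---|---|---|
| Sensitivity 75/85 | 0 | 0 | 75.0/85.0 | +10.0 | +10.0 |
| Sensitivity 75/85 | 0.3 | 0 | 72.9/83.3 | +10.0 | +10.5 |
| Sensitivity 75/85 | 0.5 | 0 | 71.1/81.9 | +10.0 | +10.8 |
| Sensitivity 75/85 | 0.7 | 0 | 69.1/80.1 | +10.0 | +11.0 |
| Sensitivity 75/85 | 0.5 | 0.2 | 71.2/80.1 | +10.0 | +9.0 |
| Sensitivity 85/85 | 0.5 | 0 | 82.0/82.0 | 0 | 0 |
| Sensitivity 85/85 | 0.5 | 0.2 | 82.0/80.2 | 0 | −1.8 |
| False positives 10/15 | 0.5 | 0.2 | 8.5/12.0 | +5.0 | +3.5 |

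The levels fall whenever readers are positively correlated. The difference can move either way or not at all.

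**The case against.** The strongest reply is that the target is the effect of CAD, a paired contrast, and that a distorted level need not distort it. This is partly right. Suppose the first reader detects 70% without and 80% with CAD, and the second detects 30% and 40% of the missed 20%. The pooled values are (0.70 + 0.20 × 0.30)/1.20 = 63.3% and (0.80 + 0.20 × 0.40)/1.20 = 73.3%: the levels are about 7 points low, but the difference is still 10. A reader might infer that the CAD test is invalid or its effect estimate necessarily biased. The documents do not support that, since the shift depends on correlations they do not give.

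A reader might also infer that truly negative images are over-weighted against cancers. They are not, because Section 13.3 tests within truth groups. What is over-weighted is the first reader's negatives within each group.

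Three points of interpretation also stand:

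- Pooling is implied by the reason given for clustering, but it is not stated.
- That the with-CAD call triggers the second reading is inferred from the reading order.
- The trigger is not identical to the tested outcome. At baseline it requires no actionable nodule and no recommended follow-up; at the annual screen only the absence of recommended follow-up. A follow-up recommendation for a non-nodule finding therefore also leaves an image with one reading.

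Finally, this analysis is outside the objectives in Section 3.0. None of this removes the contradiction. The independence needed to avoid bias in the rates also sits badly with a clustering correction, which presumes correlated readings.

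**Conclusion.** The point holds in limited form. Section 13.3 contradicts Sections 8.0 and 9.0 on who reads what. Applying the clustered test to all readings would bias the pooled sensitivity and false-positive rate downward unless readers are independent given truth group.

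At 85% single-reader sensitivity the loss in reported with-CAD sensitivity ranges from 0 to about 11 points (85 − 73.9); it is about 6 points if the second reader finds 40% of the misses. A 10% false-positive rate would appear as 5.3% to 10%. These ranges assume pooling, a with-CAD trigger, and no negative correlation between readers. If the 85% describes the two-reader programme instead, a single reader's sensitivity would be lower and more cancers would be read twice.

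Bias in the CAD contrast is possible but not established. The comparison of study arms on advanced-stage cancer does not use this test and is unaffected. The correction should be made, but the trial's main result does not depend on it.

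**What to change.** In Section 13.3:

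1. Base the CAD comparison on the first radiologist's paired readings (without, then with CAD), one pair per screened image, within each truth group.
2. Use the ordinary McNemar test for each screening round. Keep a clustered version, with the subject as cluster, only if baseline and annual images are combined.
3. Report second readings separately, labelled as conditional on a negative first reading.
4. Replace the sentence about two radiologists with one that agrees with Sections 8.0 and 9.0.

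This changes analysis wording only; the first radiologist's findings are already recorded on the Radiology Reading Form for every screened image. The small downside is that second readings leave the main CAD test: 6 of 46 cancer readings at baseline on the planning figures, and 0.90/1.90 = 47% of readings of cancer-free images at a 10% false-positive rate. Second readings of all first-reader positives, or of a random sample of them, could also support a two-reader analysis if the selection were accounted for, but would add reading work.
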